## Abstract

**Introduction:**

The Rehabilitation EnAblement in CHronic Heart Failure (REACH-HF) trial is part of a research programme designed to develop and evaluate a health professional facilitated, home-based, self-help rehabilitation intervention to improve self-care and health-related quality of life in people with heart failure and their caregivers. The trial will assess the clinical effectiveness and cost-effectiveness of the REACH-HF intervention in patients with systolic heart failure and impact on the outcomes of their caregivers.

**Methods and analysis:**

A parallel two group randomised controlled trial with 1:1 individual allocation to the REACH-HF intervention plus usual care (intervention group) or usual care alone (control group) in 216 patients with systolic heart failure (ejection fraction <45%) and their caregivers. The intervention comprises a self-help manual delivered by specially trained facilitators over a 12-week period. The primary outcome measure is patients’ disease-specific health-related quality of life measured using the Minnesota Living with Heart Failure questionnaire at 12 months’ follow-up. Secondary outcomes include survival and heart failure related hospitalisation, blood biomarkers, psychological well-being, exercise capacity, physical activity, other measures of quality of life, patient safety and the quality of life, psychological well-being and perceived burden of caregivers at 4, 6 and 12 months’ follow-up. A process evaluation will assess fidelity of intervention delivery and explore potential mediators and moderators of changes in health-related quality of life in intervention and control group patients. Qualitative studies will describe patient and caregiver experiences of the intervention. An economic evaluation will estimate the cost-effectiveness of the REACH-HF intervention plus usual care versus usual care alone in patients with systolic heart failure.

**Ethics and dissemination:**

The study is approved by the North West—Lancaster Research Ethics Committee (ref 14/NW/1351). Findings will be disseminated via journals and presentations to publicise the research to clinicians, commissioners and service users.

**Trial registration number:**

ISRCTN86234930; Pre-results.

## Introduction

Heart failure (HF) is a generally progressive condition that is estimated to affect 900 000 people in UK^1^ and is associated with significant health expenditure, amounting to around 1.0–3.2% of the total healthcare expenditure in Western Europe, North America and Latin America.^2^

People with HF experience a range of symptoms including shortness of breath at rest or on exertion, fatigue, fluid retention, impaired cognitive function and appetite disturbance.^3^
^4^ HF is categorised as either HF with reduced ejection fraction (also known as systolic HF or left ventricular systolic dysfunction), or HF with preserved ejection fraction (also known as diastolic HF). Systolic HF is due to impaired left ventricular contraction, which results in a reduced ejection fraction (usually <45%) and diastolic HF is due to stiffness of the ventricle wall delaying filling of the heart chamber.^5^

Advances in pharmacological therapies and devices (implantable cardioverter defibrillators and biventricular pacing) have been shown to improve physiological parameters and quality of life, reduce symptoms and decrease mortality and readmission rates.^5^ However, HF continues to have significant negative impacts on the quality of life of patients and their families or caregivers,^6^ remains a common cause of hospitalisation, and accounts for a substantial personal and economic burden.

Cardiac rehabilitation (CR) is a process by which patients with heart disease, in partnership with health professionals, are encouraged and supported to achieve and maintain optimal physical health.^7^ A recent Cochrane systematic review including 33 randomised trials in 4740 individuals with HF showed that participation in exercise-based CR was associated with a significant reduction in the risk of overall hospitalisation (relative risk: 0.75; 0.62 to 0.92, p=0.005) and HF-specific hospitalisation (relative risk: 0.61; 0.46 to 0.80, p=0.0004) and important improvements in patient health-related quality of life.^8^ Based on such accumulating evidence, in 2010 the UK National Institute of Health and Care Excellence (NICE) recommended offering CR based on supervised group exercise for patients with systolic and diastolic HF.^1^ Despite this recommendation, a survey in 2012 indicated that few UK centres (16% of those surveyed) had a specific rehabilitation programme for those with HF.^9^ The UK uptake of rehabilitation for people with HF therefore remains poor.^9^ A recent European survey on exercise training in HF concluded that ‘too many patients are still denied a highly recommended therapy’.^10^ We believe two key solutions to this poor provision and uptake are the development of a home-based self-help CR manual designed to meet the needs of those with HF and the close involvement of their caregivers.

The Rehabilitation EnAblement in CHronic Heart Failure (REACH-HF) research programme was designed to develop and evaluate a health professional facilitated home-based self-help manual rehabilitation intervention to improve self-care and health-related quality of life (HRQoL) in people with HF and their caregivers.

## Aims and hypothesis

This trial aims to assess the clinical effectiveness and cost-effectiveness of the addition of the REACH-HF intervention to usual care in patients with systolic HF and their caregivers. The primary hypothesis is that REACH-HF plus usual care (as received by participants in the ‘intervention group’) compared with usual care alone (as received by participants in the ‘control group’) can improve the disease specific HRQoL of patients at 12 months’ follow-up (primary outcome). Secondary objectives of the trial are:
To compare secondary outcomes between patients in the intervention and control group (comprising the composite outcome of all-cause death or HF-related hospital admission, brain natriuretic peptide levels, exercise capacity, psychological well-being, level of physical activity, generic health-related quality of life and safety);To estimate the cost-effectiveness of the REACH-HF intervention plus usual care versus usual care alone, for patients with systolic HF;To explore the moderators and mediators of change in disease-specific HRQoL of patients in intervention and control groups;To assess the impact of, acceptability and satisfaction of the REACH-HF intervention to patients and caregivers;To compare psychological well-being, quality of life, self-care activities, and burden, between caregivers in the intervention and control groups;To check the fidelity of delivery of the REACH-HF intervention to patients and caregivers.

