#### Secondary outcomes

##### Patients

Composite outcome of death or hospital admission related to HF or not related to HF. All instances of hospitalisation and death will be recorded and made accessible to an independent adjudication panel of three experienced cardiologists who will ascertain whether or not reported events are HF-related.NT pro-BNP levels. Natriuretic peptide levels are elevated in patients with HF.^16^Exercise capacity (incremental shuttle walk test (ISWT)).^17^Physical activity level (accelerometry over a 7-day period, measured using the GENEActiv Original accelerometer).^18^Psychological well-being using Hospital Anxiety and Depression Scale questionnaire (HADS).^19^Generic HRQoL using the EQ-5D-5L questionnaire.^20^Disease-specific quality of life using the Health-related Quality of Life (HeartQoL) questionnaire.^21^Self-care of HF Index questionnaire (SCHFI).^22^Healthcare utilisation (ie, primary and secondary care contacts, social care contacts and relevant medication usage).Self-efficacy for key behaviours questionnaires (developed by the research team).Safety; recording and reporting of serious adverse events. Any adverse event or adverse reaction will be regarded as serious if it: results in death, is life-threatening, requires hospitalisation or prolongation of existing hospitalisation, results in persistent or significant disability or incapacity. All serious adverse events that occur during the trial will be recorded and reported to the Ethics Committee, the Data Monitoring Committee and the Trial Steering Committee.

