### Data analysis

#### Primary and secondary outcomes

All analyses, quantitative and qualitative, will be conducted according to best practise and reported in accordance with Consolidated Standards of Reporting Trials (CONSORT) guidelines for reporting of clinical trials^31^ and appropriate guidelines for reporting process evaluations^32^ and qualitative research.^33^ Baseline sociodemographic and health-related variables will be reported descriptively by treatment arm, in order to assess whether the inferential analyses require adjustment for any unbalanced variables.

The primary analyses for all patient and caregiver outcomes will be based on a between-group, intention-to-treat, complete case approach, using data collected at 12 months’ follow-up. The outcomes will be analysed using the regression method appropriate to the data, that is, linear regression modelling for continuous outcomes, survival analysis based on the Cox proportional hazards regression model for time-to-event data, and Tobit regression analysis for EQ-5D-5L. All analyses will adjust for baseline score of the outcome variable (where applicable), as well as minimisation variables previously described, and sociodemographic and health-related variables that are found to be unbalanced at baseline.

Secondary analyses will be undertaken on patient and caregiver outcomes as repeated measures analysis using all follow-up assessment points (4, 6 and 12 months). In addition, a per protocol analysis of the primary outcome will be performed using 12-month follow-up data. A per protocol definition (based on a minimum level of intervention uptake and adherence deemed necessary to achieve improvement in outcomes) will be agreed prior to the start of data analysis. If there is more than 5% loss to follow-up for the primary outcome at 12 months, multiple imputation methods will be used as a sensitivity analysis to address the issue of missing data. The following subgroups will be assessed: the stratification variables of trial centre and severity of HF (NT pro-BNP levels), plus time since HF diagnosis and the inclusion (or not) of a caregiver.

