The potential for differential intervention effects within patient subgroups (ie, moderation by patient characteristics) will be explored using interactions within linear regression modelling for the primary outcome only. Mediation analyses will be used to assess the extent to which secondary outcomes at intermediate follow-up (eg, self-efficacy or physical activity levels at 4 months) or progress tracker self-care behaviours (eg, self-reported exercise, stress or anxiety management activities) can explain between-group differences in the primary outcome at 12 months. Moderation and mediation analyses will be exploratory in nature as no formal power calculation for interaction effects has been performed.

Serious adverse events will be presented descriptively by treatment arm.

All between group outcome results will be presented as means and 95% CIs. No correction of p values for multiplicity of testing will be undertaken. However, the primary outcome (MLHFQ at 12 months) analysis will be performed before all other analyses and the p values of all subsequent analyses interpreted in the context of multiple testing. No interim analyses will be performed. All analyses will be conducted by a statistician who is blinded to treatment arm, using Stata V.12.

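### Safety is to be compared between groups, but the only analysis stated for serious adverse events is descriptive by arm, so no between-arm estimate or interval is planned for them as such

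*Protocol article*

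**What the plan says.** All references are to the Protocol article.

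- **Aims and hypothesis.** One secondary objective is "To compare secondary outcomes between patients in the intervention and control group". The list that follows ends with "level of physical activity, generic health-related quality of life and safety". Its composite is all-cause death or an admission related to heart failure (HF).
- **Secondary outcomes, Patients.** Safety is a listed secondary outcome: "Safety; recording and reporting of serious adverse events". An event is serious if it "results in death, is life-threatening, requires hospitalisation or prolongation of existing hospitalisation, results in persistent or significant disability or incapacity". The composite is worded differently here: "Composite outcome of death or hospital admission related to HF or not related to HF".
- **Data analysis, Primary and secondary outcomes.** The primary analyses of all patient outcomes are between-group and by intention to treat. The methods named are linear regression for continuous outcomes, "survival analysis based on the Cox proportional hazards regression model for time-to-event data", and Tobit regression for EQ-5D-5L. Between-group results are to carry 95% CIs. Serious adverse events have their own sentence: "Serious adverse events will be presented descriptively by treatment arm".

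**The concern.** The objective and the analysis do not match. Safety is one of the outcomes to be compared, yet the one sentence on how serious adverse events will be analysed calls for description by arm. None of the named regression methods is for the proportion of patients with an event.

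What is at stake is how the safety result will be read. The intervention includes a home-based exercise programme for patients with an ejection fraction below 45%. Two similar percentages printed without an interval can be taken as reassurance. In a trial of this size, similar percentages are compatible with a sizeable excess in the intervention arm, and a descriptive table does not show how large that excess could be.

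**Working it through.** **1. The plan's own figure.** The trial is sized on the primary outcome only (Sample size section: difference 5 points, SD 10, type I error 0.05, power 90%). Two-sided:

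n per group = 2 × (1.960 + 1.282)² × 10² / 5² ≈ 84.1, rounded up to 85, as stated.

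For 20% attrition, 85 / 0.80 = 106.25, so 107, and 86 / 0.80 = 107.5, so 108. The stated 108 per group (216 in total) is reproduced to within one patient. No event rate, margin or power is given for safety.

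**2. What the composite covers.** Set the criteria for a serious event against the two wordings of the composite:

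| Criterion for a serious event | Composite in Aims and hypothesis | Composite in Secondary outcomes |
|---|---|---|
| Death | covered | covered |
| HF-related admission | covered | covered |
| Other admission | not covered | covered |
| Life-threatening or disabling, no admission | not covered | not covered |

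A Cox analysis would give a hazard ratio with an interval for the covered rows. It would not give one for serious adverse events as a whole. If it is run as time to first event, repeat events are also outside it.

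**3. What an interval would show.** The documents give no serious adverse event rate, so the risks below are assumptions. With the same observed risk p in both arms and 108 per arm, the Wald half-width is 1.96 × √(2p(1−p)/108). At p = 0.20 this is 1.96 × √(0.32/108) = 1.96 × 0.0544 = 0.107.

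| Assumed risk in both arms | Upper 95% limit for excess, Wald (points) | Newcombe (points) |
|---|---|---|
| 5% | 5.8 | 6.3 |
| 10% | 8.0 | 8.4 |
| 20% | 10.7 | 10.8 |
| 30% | 12.2 | 12.0 |
| 40% | 13.1 | 12.8 |
| 50% | 13.3 | 13.1 |

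With 86 per arm (about 20% attrition) the Wald limits run from 6.5 to 14.9 points.

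**4. An unequal example, also assumed.** For 20% in control and 25% in intervention: SE = √((0.20×0.80 + 0.25×0.75)/108) = √(0.3475/108) = 0.0567. The interval is 0.05 ± 0.111, that is −6.1 to +16.1 points.

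**5. The composite is imprecise too.** If the hazard ratio is observed at 1, its upper 95% limit is about exp(1.96 × 2/√d) for d events in total: 2.40 with 20 events, 1.86 with 40, 1.66 with 60, 1.55 with 80 and 1.48 with 100. The event numbers are assumed.

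**The case against.** The strongest reply has four parts.

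- **The composite already gives an interval.** Deaths and admissions are two of the criteria for a serious event, and on the wording under Secondary outcomes all of them enter the Cox analysis. This stands in large part. A reader might infer that the trial will give no between-arm estimate of serious harm at all, and the document does not support that. What remains is that no estimate is stated for serious adverse events as such, and that the coverage turns on an unresolved definition.
- **Readers can work out the interval.** If patient counts and denominators are printed by arm, anyone can compute a risk difference and CI. This also stands. It would be wrong to say that the trial cannot bound the excess harm; the accurate statement is that the plan does not say it will report that bound. A table of event counts alone, without patients affected, would not allow the calculation.
- **Descriptive need not mean descriptive only, and detail belongs in the statistical analysis plan.** The article does not use the word only, it has a general rule for between-group results, and descriptive reporting of serious adverse events is common in trials of this size. This lowers the weight of the point. But the article does not leave the matter open: it gives serious adverse events their own analysis sentence, and that sentence does not deliver the comparison in the objective.
- **Safety is handled elsewhere.** Patients with contraindications to exercise are excluded, trained facilitators may stop delivery for undue harm, and an independent Data Monitoring Committee reviews safety. All true. These measures protect participants during the trial; they do not supply the between-arm estimate at its end. It would go too far to call the programme unsupervised, since it is facilitated by cardiac nurses or physiotherapists.

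**Conclusion.** The concern holds as a modest mismatch between objective and analysis. Safety is to be compared, serious adverse events are to be described by arm, and no between-arm difference or interval is planned for them as such. The Cox analysis of death or admission fills part of the gap, more under the wording in Secondary outcomes than under that in Aims and hypothesis.

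The size is an illustration: identical observed risks would leave an excess of about 6 to 13 percentage points compatible with the data. It rests on assumed risks of 5% to 50%, 108 patients per arm and standard 95% intervals. The imprecision comes from the sample size and exists whether or not the interval is printed; printing it makes it visible. Nothing here indicates that the intervention is harmful, and the primary analysis is unaffected.

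**What to change.** In Data analysis, Primary and secondary outcomes, extend the sentence on serious adverse events along these lines: the number and percentage of patients with at least one serious adverse event will be given for each arm, analysed as randomised, with the risk difference and its 95% CI; no significance test will be done, and safety will not be inferred from an interval that includes zero; event types will be listed descriptively by arm.

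The data are already collected from baseline to the final follow-up visit, so the cost is one line of text and one table row. The downside is a wide interval and a more guarded safety statement.

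The minimum alternative is to reword the objective so that safety is described by arm and not compared. That removes the mismatch but gives the reader less. The two wordings of the composite should be reconciled in any case, because they determine how much of serious harm the Cox analysis covers.

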## Methods and analysis

This protocol is reported in accord with the Standard Protocol Items: Recommendations for Interventional Trials (SPIRIT) 2013 guidance for protocols of clinical trials.^11^

### Design

The study is a multicentre parallel two group randomised superiority trial with individual participant allocation to intervention group or control group with nested process and health economic evaluations. Given the complex nature of the intervention, it is not possible to blind participants or those involved in the provision of care. Researchers undertaking collection of outcome data and the statistician undertaking the data analysis will be blinded to treatment allocation in order to minimise potential bias. An illustration of the study flow is given in figure 1.

**Figure 1 BMJOPEN2015009994F1:**
[figure not shown]
Illustration of study flow.

### Setting

The study will be conducted in four investigator centres in the UK: Birmingham (Sandwell and West Birmingham Hospitals NHS Trust), Cornwall (Royal Cornwall Hospitals NHS Trust), Gwent (NHS Wales) and York (York Teaching Hospital NHS Foundation Trust). Participants will be recruited at each of the four sites. To achieve adequate participant enrolment to sample size, each site can recruit through either primary or secondary care pathways, with each site having the opportunity to implement secondary strategies depending on recruitment performance which will be formally reviewed periodically by the central trial management team. Follow-up procedures will be conducted on NHS and non-NHS premises. Conduct of the study at each centre will be led by a local Principal Investigator supported by a research nurse(s) who has received training in Good Clinical Practice and in the requirements of the study protocol. Each participating site is responsible for the recruitment and scheduled follow-up visits of participants.

### Study population

The study population includes patients and caregivers. Participating patients will be aged 18 years or older and have a confirmed diagnosis of systolic HF on echocardiography or angiography (ie, left ventricular ejection fraction <45% within the past 5 years). Patients who have undertaken CR within 12 months prior to enrolment will be excluded, as will patients contraindicated to exercise testing or exercise training (adjudged according to adapted European Society of Cardiology guidelines for HF).^12^ The complete list of patient inclusion and exclusion criteria is provided in box 1.
Box 1Trial entry criteriaInclusion criteriaProvision of informed consent to participate.Adults (aged ≥18 years).Patients who have a confirmed diagnosis of systolic heart failure (HF) on echocardiography (ie, left ventricular ejection fraction <45% within the past 5 years).Patients who have experienced no deterioration of HF symptoms in the past 2 weeks resulting in hospitalisation or alteration of HF medication*Exclusion criteria*
Patients who have undertaken cardiac rehabilitation (CR) within the past 12 monthsPatients who have received an intracardiac defibrillator (ICD), Cardiac Resynchronisation therapy (CRT) or combined CRT/ICD device implanted in the last 6 months.Patients who have any of the following contraindications to exercise testing or exercise training documented in their medical notes:
Early phase after acute coronary syndrome (up to 2 days)Untreated life-threatening cardiac arrhythmiasAcute HF (during the initial period of haemodynamic instability)Uncontrolled hypertension (systolic blood pressure >200 and/or diastolic blood pressure >100)Advanced atrioventricular blockAcute myocarditis and pericarditisSymptomatic aortic stenosisSevere hypertrophic obstructive cardiomyopathyAcute systemic illnessIntracardiac thrombusProgressive worsening of exercise tolerance or dyspnoea at rest over previous 3–5 daysSignificant ischaemia during low-intensity exercise (<2 Metabolic equivalents, <50 Watts)Uncontrolled diabetes (blood glucose >16 mmol/L or glycated hemoglobin >9% or equivalent unit)Recent embolismThrombophlebitisNew-onset atrial fibrillation/atrial flutterPatients who are in a long term care establishment or who are unwilling or unable to travel to research assessments or accommodate home visits.Patients who are unable to understand the study information or unable to complete the outcome questionnaires.Patients judged to be unable to participate in the study for any other reason (eg, psychiatric disorder, diagnosis of dementia, life threatening co-morbidity)Patients participating in concurrent interventional research which may over-burden the patient or confound data collection.

Participating caregivers will be aged 18 years or older and provide unpaid support to patients who could otherwise not manage without such support. Unpaid support includes emotional support, prompting with taking medications, observing for signs and symptoms of HF, getting prescriptions, encouraging participation in social events and physical activity, helping with household tasks or providing physical care.

A patient may still participate if s/he does not have an identified caregiver, or if the patient's caregiver is not willing to participate. Similarly patients who are unable or not willing to undertake the exercise capacity assessment will not be excluded.

Participants are free to withdraw from the study at any time, and this will be emphasised during the consent process. If a participant chooses to withdraw they will be asked to provide a reason and the reason for withdrawal will be noted. Participants do not have to provide a reason and this will be reiterated by the PI (or authorised delegate) in the event of a withdrawal request. Data collected on participants prior to withdrawal will be retained for analysis.

